# 1 INTRODUCTION

## 1.1 BACKGROUND OF THE CLINICAL TRIAL

### Scientific problem

Kidney transplantation is the gold standard of treatment for patients with ESRD (End stage renal disease). After transplantation, immunosuppressive drugs are crucial for reducing the risk of organ rejection. Despite this desired effect, the compromised immunity of the recipient leads to an increased risk for infectious disease. Moreover, current immunosuppression regimens are unable to sufficiently control allo-recognition of the graft, which leads to chronic rejection. Thus, optimal management of immunosuppressive drug dosing requires a delicate balance between inadequate and excessive immunosuppression. At present, **there is no diagnostic test or algorithm for optimal guidance of immunosuppressive drugs in clinical routine.** Monitoring relies on the quantification of calcineurin inhibitors trough levels, mostly tacrolimus (TAC), in the peripheral blood, which correlate more closely with the risk of drug-related toxicity than with the effectiveness of immunosuppression. There is an urgent need for tools to personalize immunosuppression in order to reduce the risk of infectious disease and, at the same time, graft rejection.

### Status of the research

**While most of the proposed assays focus on graft rejection, a useful approach for guidance of immunosuppression would ideally predict both graft rejection and infectious disease.** To address this, two assays were proposed. A test of leucocyte function, the QuantiFERON Monitor (Qiagen), was prognostic for infectious events, but not for graft rejection in kidney, liver and lung transplant patients (Mian et al. Clin Infect Dis. 2018). In a randomized controlled trial, tailoring immunosuppression after liver transplantation via assessment of CD4+ lymphocyte function using Immuknow® (Erofins Viracor) resulted in fewer infectious events, but had no influence on graft rejection (Ravaioli et al. Transplantation. 2015). However, the trial design precluded reliable analysis concerning safety and efficacy. Currently, no further interventional trials in solid organ transplantation are registered for either of these products or for other tools capable of quantifying immune function in a clinically useful manner.

Recently, no major safety signal was observed in a German multicenter, open-label randomized, controlled trial in pediatric kidney recipients testing the steering of immunosuppressive therapy by levels of virus-specific T cells (adenovirus, cytomegalovirus, and herpes simplex virus quantified by cytokine flow cytometry; Ahlenstiel-Grunow et al. JASN. 2021). No difference was observed in rejection and infection, which were part of the secondary analysis. Of note, the complexity of virus-specific T cell monitoring poses a major obstacle for further efficacy trials and introduction in the clinical routine.

### Torque Teno virus

**Monitoring TTV in peripheral blood is a promising new strategy for quantifying immune function** (De Vlamincx et al. Cell. 2013; Focosi et al. Clinical microbiology and infection. 2016). TTV can be detected in up to 90% of healthy individuals and has not been linked to any human disease. Peripheral blood copy numbers of **TTV are associated with the function of the immune system of the host.** The prevalence of TTV in patients after transplantation is around 99% and the virus is unaffected by conventional anti-viral drug therapy used in the post-transplantation setting. TTV copy number is directly associated with factors determining the immune function including age, sex and the amount and type of immunosuppressive drugs

administered to transplant recipients and is thus indirectly associated with graft rejection and infectious disease.

**Quantification of TTV represents a novel approach for the assessment of the human immune system.** Instead of characterizing single compartments of the immune system, TTV copy number might be able to mirror the function of the host's immune system in a more holistic aspect. Besides T cells, other major components of the immune system are involved in TTV control: NK cells, antigen-presenting cells, B cells, the complement system, pattern recognition receptors and antibodies.

**We and others have demonstrated the predictive value of TTV copy number for infectious disease and organ rejection in kidney allograft recipients.**

### **Preliminary data**

In a prospective study, we analysed 169 consecutive kidney transplant recipients and found that the risk for infectious disease could already be stratified by TTV 3 months before the event (median  $4 \times 10^8$  copies/mL [c/mL], interquartile range [IQR]  $3 \times 10^7$ - $2 \times 10^9$  for infections vs.  $3 \times 10^7$ , IQR  $1 \times 10^6$ - $7 \times 10^8$  for non-infections), whereas routine clinical markers, including level of immunosuppressive drugs, were not predictive (Strassl et al. The Journal of Infectious Diseases. 2018). Colleagues from Spain have confirmed our findings (Fernandez-Ruiz et al. American Journal of Transplantation. 2019). In a cohort study, we analysed 113 kidney transplant patients and described the predictive value of TTV for clinically overt acute rejection (Strassl R et al. The Journal of Infectious Diseases. 2019). Conventional markers were non-predictive, but TTV copies were predictive for rejection more than one month before diagnosis was made by indication biopsy (rejection: median  $3 \times 10^7$  c/mL, IQR  $5 \times 10^5$ - $2 \times 10^8$  vs. no rejection:  $2 \times 10^8$ , IQR  $1 \times 10^7$ - $4 \times 10^9$ ).

In direct preparation for this trial, we re-analysed TTV in all consecutive kidney graft recipients transplanted at the MUV between 2016 and 2018 and confirmed the predictive value of TTV for infectious disease and clinically overt rejection in 386 patients (Doberer K et al. American Journal of Transplantation. 2020). Each log increase in TTV load decreased the odds for rejection by 22% (odds ratio [OR] 0.78, 95% confidence interval [CI] 0.62-0.97;  $p=0.027$ ) and increased the odds for infection by 11% (OR 1.11, 95% CI 1.06-1.15;  $p<0.001$ ). TTV was quantified at a median of 14 days before rejection was diagnosed and 27 days before onset of infection. Patients with allograft rejection had lower levels of TTV compared to patients without rejection (median  $3.5 \times 10^6$  c/mL, IQR  $1.7 \times 10^5$ - $1.3 \times 10^8$  c/mL vs. median  $2.5 \times 10^8$  c/mL, IQR  $5.8 \times 10^6$ - $9.3 \times 10^8$  c/mL, respectively;  $p=0.028$ ) in subsequent biopsies. Applying receiver operating characteristic curve, an area under the curve of 0.73 (IQR, 0.54-0.92;  $p=0.028$ ) was calculated to classify rejection by TTV level. A TTV level cut-off of  $1.5 \times 10^6$  c/mL corresponded to a specificity of 89% and a sensitivity of 36%, a negative predictive value (NPV) of 77% and a positive predictive value (PPV) of 50%. For TTV levels above  $10^7$  c/mL, high NPVs (range 84% to 87%) were calculated, and PPVs were high below a TTV level of  $10^5$  c/mL (range 57% to 85%). Higher levels of TTV were detected in the plasma drawn from individuals experiencing an infectious event in the subsequent observation period compared to patients without infection (median  $3.9 \times 10^8$  c/mL, IQR  $7.9 \times 10^6$ - $3.3 \times 10^9$  c/mL vs. median  $2.6 \times 10^7$  c/mL, IQR  $1.3 \times 10^6$ - $9.2 \times 10^8$  c/mL, respectively;  $p<0.001$ ). Further subgroup analysis showed a comparable effect size for the association between TTV level and infections that did not require hospitalisation (OR 1.10, 95% CI 1.04-1.16,  $p<0.001$ ). The largest effect size was calculated for BK infections (presumptive polyomavirus-associated nephropathy [PVAN] and PVN; OR 1.21, 95% CI 1.06-1.39,  $p=0.005$ ), followed by cytomegalovirus (CMV) disease (CMV syndrome and end-organ disease; OR 1.16, 95% CI

1.05-1.27,  $p=0.005$ ) and infections restricted to opportunistic pathogens (OR 1.16, 95% CI 1.07-1.26,  $p<0.001$ ). A smaller effect size was found for infections with extracellular bacteria (OR 1.06, 95% CI 1.00-1.12,  $p=0.05$ ). Applying receiver operating characteristic curve, an area under the curve of 0.62 (IQR, 0.58-0.67;  $p<0.001$ ) was calculated to classify infection by TTV level. A TTV level  $>5.8 \times 10^9$  c/mL corresponded to a specificity of 90%, a sensitivity of 18%, an NPV of 77% and a PPV of 37% to detect infection. For TTV level up to  $10^9$  c/mL, high NPVs were calculated for the detection of infection (range 79% to 100%), and the highest PPV was calculated for TTV loads above  $10^{10}$  c/mL (range 44% to 67%).

In an addition study we analysed 82 protocol biopsies from month 12 after transplantation from clinically stable kidney transplant recipients transplanted consecutively in 2017 and 2018 at the MUV and confirmed the predictive value of TTV in this setting (Doberer et al. Transplantation. 2021). Patients with graft rejection had a lower TTV load than patients without rejection (median  $2 \times 10^5$  c/mL, IQR  $3 \times 10^3$ - $2 \times 10^6$  vs.  $7 \times 10^5$  c/mL, IQR  $1 \times 10^5$ - $2 \times 10^7$ ). Each log increase in TTV load decreased the risk for rejection by 9% (RR 0.91, 95% CI 0.85-0.97;  $P=.004$ ). Interestingly, the time TTV measurements were below  $1 \times 10^6$  c/mL between months 3 and 12 post-transplant was associated with the development of chronic lesions in the month 12 biopsies as compared to month 3 protocol biopsies: the longer the TTV c/ml was below  $1 \times 10^6$ , the more likely lesions would be observed in the month 12 biopsy (coefficient 0.07, 95% CI 0.01-0.14;  $P=.02$ ).

### 1.1.1 NAME AND DESCRIPTION OF THE INVESTIGATIONAL PRODUCTS

#### General considerations

Within the active/interventional group TAC will be dosed supported by TTV load in the plasma quantified by the real-time PCR detection and quantification kit, TTV R-GENE®. TAC is approved for its intended use in this clinical study by all national competent regulatory authorities of the participating countries, and the TTV R-GENE® is CE certified. The intervention itself is restricted to a novel dosing strategy for TAC according to TTV load quantified by TTV R-GENE®. For details see 5.1.

#### Tacrolimus

TAC is a macrolide calcineurin inhibitor. TAC is indicated for the prophylaxis of organ rejection, in adult and pediatric patients receiving allogeneic kidney, liver transplants and heart transplants, in combination with other immunosuppressants. TAC is approved for its intended use in this clinical study by all national competent regulatory authorities of the participating countries.

**The TTV R-GENE®**, using the real-time PCR technology after extraction of the viral DNA, enables to detect and quantify the genome of TTV in whole blood, plasma and serum samples. The kit is intended for in vitro diagnostic use only, in clinical laboratories by laboratory health professionals. The TTV R-GENE® is CE certified.

## 1.2 RATIONALE OF THE CLINICAL TRIAL

**The specific aim of the proposal is to demonstrate the safety and tolerability of TTV-guided immunosuppression in kidney transplant recipients. For the first time, a comprehensive, personalised and functional assessment of the immune system will be tested in a randomised and controlled clinical setting.**

Kidney transplantation is the gold standard of treatment for patients with ESRD. After transplantation, immunosuppressive drugs are crucial for reducing the risk of organ rejection.

Despite this desired effect, the compromised immunity of the recipient leads to an increased risk for infectious disease. Moreover, current immunosuppression regimens are unable to sufficiently control allo-recognition of the graft, which leads to chronic rejection. Thus, optimal management of immunosuppressive drug dosing requires a delicate balance between inadequate and excessive immunosuppression. **At present, there is no diagnostic test or algorithm for optimal guidance of immunosuppressive drugs in clinical routine.**

**The proposed clinical trial will assess the potential of a novel healthcare intervention that would generate meaningful advances in clinical practice and care for patients with ESRD. Notably, the trial would enable clinicians to personalise and optimise immunosuppressive drug dosing and thus reduce infections and graft rejection in kidney transplant recipients. Both outcomes are burdensome for kidney transplant patients and highly clinically relevant. Infections are the second-most common cause of death following kidney transplantation and rejection is the leading cause of graft loss.**

### 1.3 BENEFIT-RISK ASSESSMENT

#### 1.3.1 SUMMARY OF THE KNOWN AND POTENTIAL RISKS AND BENEFITS, IF ANY, TO HUMAN SUBJECTS.

##### General considerations

Non-interventional studies have suggested that measurement of TTV load in the peripheral blood of kidney transplant recipients is superior compared to standard TAC trough level-based risk prediction of harmful effects due to insufficient or excessive immunosuppression in the first year post-transplantation. However, no interventional study has tested the safety or efficacy of TTV-guided immunosuppression. **Taken together, non-interventional studies provide sufficient scientific evidence to use TTV-guided immunosuppression, but genuine uncertainty about the safety, tolerability and effectiveness warrant an interventional trial.**

##### Risk of trial therapy

Within the trial TAC will be dosed supported by TTV quantification. Adverse reactions of TAC are well known and described. We do not expect other adverse reactions. In worse case a higher rate or intensity of these adverse reactions might occur.

The most common adverse reactions observed in TAC-treated kidney transplant patients are: infection, tremor, hypertension, abnormal renal function, constipation, diarrhoea, headache, abdominal pain, nausea, asthenia, pain, insomnia, peripheral oedema, hypomagnesemia, hypophosphatemia, hyperlipidaemia, hyperkalaemia, and anaemia.

- Patients receiving TAC, are at increased risk of developing lymphomas and other malignancies, particularly of the skin. Post-transplant lymphoproliferative disorder has been reported in immunosuppressed organ transplant recipients. Cases of pure red cell aplasia have been reported in patients treated with TAC.
- Patients receiving TAC are at increased risk of developing bacterial, viral, fungal and protozoal infections, including opportunistic infections. These infections may lead to serious, including fatal, outcomes. Serious viral infections reported include PVAN, mostly due to BK virus infection and CMV infections.
- TAC was shown to cause new onset diabetes mellitus.
- TAC can cause acute or chronic nephrotoxicity.

- TAC may cause a spectrum of neurotoxicities. The most severe neurotoxicities include posterior reversible encephalopathy syndrome, delirium, seizure and coma; others include tremors, paresthesias, headache, mental status changes, and changes in motor and sensory functions.
- Hyperkalaemia has been reported with TAC. Hypertension is a common adverse effect of TAC therapy. TAC may prolong the QT/QTc interval and may cause Torsade de Pointes. Myocardial hypertrophy has been reported.

TAC will be administered oral. If oral administration is not possible intravenous application will be used. The TAC dosage regimen is detailed in 5.7

### **Risk of trial interventions**

No additional invasive procedures such as venous puncture or allograft biopsy, will be performed for study purposes only. Protocol biopsies will be performed only where established as part of the clinical routine. Sampling for TTV quantification will be performed at routine blood draws without requiring an additional venous puncture. The amount of additional blood drawn at a single visit is not expected to cause harm to the participant.

### **Specific measures to reduce participant risk during the trial have been implemented:**

- Immunological high-risk patients will be excluded.
- TAC related AE will be assessed rigorously throughout the trial.
- An independent DSMB (Data Safety Monitoring Board) will regularly check whether predefined safety margins, sample size assumptions and rates of recruitment and loss to follow-up are met, as well as whether the level of data quality and protocol compliance is sufficient. For details see 7.4.

### **Benefit of trial therapy**

We and others have demonstrated the predictive value of TTV copy number for infectious disease and organ rejection in kidney allograft recipients (Strassl et al. The Journal of Infectious Diseases. 2018 and 2019; Fernandez-Ruiz et al. American Journal of Transplantation. 2019; Doberer K et al. American Journal of Transplantation. 2020 and Transplantation 2021). **Within the proposed trial we anticipate a reduction from infection and rejection from 40% to 30%.**

**The results of the proposed trial have the potential to change clinical practice of immunosuppression dosage after kidney transplantation, thereby reducing infectious and immunologic complications.** Effective project management, rigorous quality assurance and control and detailed risk assessment will increase the likelihood of a successful conduction of the trial and scientific integrity of the data.

Lower infection and rejection rates achieved through optimisation of immunosuppression would result in reduced hospitalisation and harm due to the side effects of antimicrobial and anti-rejection therapy. The prolongation of graft survival reduces the need for dialysis, which is a very burdensome procedure for ESRD patients, and thus improves quality of life. Improved graft survival would also reduce the number of patients re-entering the waiting-list for a kidney transplant after terminal graft failure, thereby shortening the waiting-time for ESRD patients on the waiting list for a suitable kidney. These changes would result in significant improvement in health-related quality of life for ESRD patients.

The results of the trial have the potential to contribute to increase patient and graft survival and thus to reduce the socioeconomic burden of ESRD for healthcare systems.

**Taken together, non-interventional data support the hypothesis of the trial and equipoise for the suggested intervention is given, the potential benefits outweigh the potential risks for the participants and the trial has the potential to improve clinical practice.**

## 2 OBJECTIVES OF THE CLINICAL TRIAL

### 2.1 PRIMARY OBJECTIVE

**The primary objective of the clinical trial is to demonstrate non-inferiority with respect to safety, tolerability and preliminary efficacy of TTV-guided immunosuppression compared to standard TAC dosing in stable adult kidney transplant patients with low immunological risk in the first year after transplantation.**

For the first time, a holistic personalised and functional assessment of the immune system will be tested in a randomised and controlled clinical setting.

### 2.2 SECONDARY OBJECTIVES

The secondary objective of the clinical trial is the assessment of TTV-guided immunosuppression in stable adult kidney transplant patients with low immunological risk in the first year after transplantation on kidney function, transplant rejection detected by protocol biopsy at month 12 post-transplantation, development of *de novo* DSA, number of unscheduled emergency hospital visits, admissions to the inpatient ward, development of malignoma, health related quality of life and drug adherence.

## 3 DESCRIPTION OF THE CLINICAL TRIAL

### 3.1 TRIAL DESIGN

Randomized, controlled, interventional, two arm, non-inferiority, patient and assessor blinded, multinational, and investigator driven phase II trial to compare the safety, tolerability and preliminary efficacy between standard and Torque Teno virus-guided immunosuppression in stable adult kidney transplant recipients with low immunological risk in the first year after transplantation.

### 3.2 PRIMARY END POINT

**A composite of one of the following:**

1. **Infectious disease event** (diagnosed on the basis of the Infectious Diseases Guidelines 2019 published by the American Society of Transplantation) requiring one of the following:
  - a) Inpatient treatment (including day-care)
  - b) Application of anti-bacteria, fungal, viral and protozoal drugs (including increase of prophylactic treatment dose; therapy restricted to topical treatment of minor localised cutaneous disease is excluded)
  - c) Reduction of immunosuppression

SARS-CoV-2 positive antigen test or PCR with or without COVID-19 is excluded

2. **Allograft rejection** detected upon indication biopsy, based on the Banff 2019 Kidney Meeting Report including borderline rejection suspicious for T-cellular mediated rejection (BL TCMR)
3. **Death**
4. **Graft loss**

For the primary end point analysis all episodes of infection and allograft biopsy will be re-assessed by personnel blinded to the randomization code (infection: two infectious disease specialists; biopsy: two kidney pathologist; the two assessors have to agree on one diagnosis). For this purpose biopsy slides will be made electronically available for the assessor by scanning. Infections will be evaluated according to the data provided in the eCRF, which will be recorded according to the protocol. The monitor will screen for non-reported episodes of infections. Routine calls and patient diaries will help to detect episodes of infections.

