### 5.7 INSTRUCTIONS FOR DOSE ADJUSTMENT

#### Background:

Applying the Vienna in-house PCR an increased risk for allo-graft rejection and infection was described for a TTV load outside of 6 log10 c/ml to 8 log10 c/ml in month 4 to 12 after kidney transplantation (Doberer K et al, American Journal of Transplantation, 2020). Applying this range to all available samples in the cohort described in the above cited publication in the same period, 41% of the measurements were below and 29% above the range. An upper cut-off of 7.6 log10 c/ml scored 38% of the samples above the range and thus leads to a more equal distribution (unpublished data). In preparation for this trial, we re-analysed TTV in the above

mentioned cohort using the Vienna in-house PCR and the PCR applied during the trial - the TTV R-GENE® assay - in parallel (unpublished data). The two assays were highly associated (slope: estimate 0.91, 95% CI 0.89 to 0.93; R 0.91) and the Bland-Altman plot revealed a mean difference of 1.4 log10 c/ml (95% CI of from -2.9 to 0.2). Applying this number the optimal TTV range for the trial was set at 4.6 log10 c/ml to 6.2 log10 c/ml.

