### 5.7.1 ACTIVE/INTERVENTION GROUP

#### 5.7.2 MAIN PRINCIPLES

**TTV-guided TAC dosing:** The TAC trough level target will be adapted according to TTV copies per milliliter (c/mL) in the plasma (quantified by TTV R-GENE®) at study visit 1 to 6. The target TTV load ranges from 4.6 log10 c/mL to 6.2 log10 c/mL as defined by TTV R-GENE® (=optimal range). TAC dosing according to TTV is detailed in Figure 3

**1. If TTV is not within the optimal range, the TAC trough level target has to be adapted by one step up or down compared to the current TAC trough level.**

If TTV is below the optimal TTV range, the TAC trough level target has to be increased by one step compared to the current TAC trough level, if TTV is above the optimal TTV range, the TAC trough level target has to be decreased by one step compared to the current TAC trough level.

**2. One TAC trough level adaption step is defined as 2 ng/mL (investigators are allowed to target a range of +/-1 ng/mL; thus one step might be within a minimum of 1 ng/mL and a maximum of 3 ng/mL).**

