### 5.7.3 ADDITIONAL RULES

- **All changes in TAC dose (including all non-study visits) must be performed according to the study protocol and the current TAC trough level target.**
- **TAC adaptations have to be made within 48 hours after the receipt of the TTV load.**
- **The lowest TAC trough level target is 3.5 ng/mL, the highest is 10 ng/mL.**
- **The treating physician can request additional TAC trough levels at any time (also on non-study visits) but TTV load will only be assessed and TAC trough level target changes only performed at the study visits.**
- **If non-adherence is suspected, no increase in TAC trough level target will be performed:** E.g. a failure of TAC intake more than once per week on average for b.d. and once every two weeks on average for o.d. formulation detected by the patient diary. In this case the patient should be educated about medical adherence (e.g. psychological counseling) and the target TAC trough level will not be changed according to TTV load until the next study visit.

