### 5.7.6 CONTROL GROUP

**TAC will be dosed according to TAC trough target levels defined by the local centre standard.** TAC will be quantified at every study visit. Additional TAC quantification may be ordered by the treating physician at any time.

The TTV load will be accessed but not revealed to the investigator. TTV results must not be entered in the hospital data system used for routine care but have to be entered in the eCRF by the personnel, who performed the TTV assessment. TTV results in the eCRF will only be visible for the treating clinical personnel in the active/interventional group.

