## **6.19 RESCUE THERAPY**

Kidney transplant rejection and infections will be treated in accordance to local centre standard therapy.

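### Endpoint criterion 1c (infection requiring less immunosuppression) can be met unequally in the two arms, because tacrolimus reduction follows different rules in each

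*Protocol*

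**What the plan says.** Under section 3.2, an infectious event is a primary event if it requires any one of three things: inpatient or day-care treatment (1a), antimicrobial drugs (1b), or "c) Reduction of immunosuppression" (1c).

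The rules for reducing TAC differ by arm:

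- **TTV-guided arm.** Section 5.7.2 says that "if TTV is above the optimal TTV range, the TAC trough level target has to be decreased by one step". Section 5.7.3 adds that "TTV load will only be assessed and TAC trough level target changes only performed at the study visits", and that any dose change at other times must follow the current target. Study visits are six weeks apart.
- **Exceptions in that arm.** Section 5.7.5 covers rejection, severe infection (life- or organ-threatening) and relevant BK virus infection. The investigator may then leave TTV guidance or, if it continues, apply modified rules. Section 6.21 also ends trial therapy when the investigator judges that continuing is not in the subject's best interest.
- **Control arm.** Section 5.7.6 says that "TAC will be dosed according to TAC trough target levels defined by the local centre standard". No visit-only limit is stated.
- **Both arms.** Section 6.19 says that "Kidney transplant rejection and infections will be treated in accordance to local centre standard therapy". Section 5.7.7 keeps corticosteroids and antimetabolites outside TTV guidance and encourages a stable antimetabolite dose.

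Investigators know the allocation (5.11.1). All infections are documented as adverse events (6.17), and the adverse event record includes the action taken on the investigational product, with dose reduction as one option (7.2). Two blinded infectious disease specialists judge each infection from the eCRF (3.2).

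**The concern.** Criterion 1c describes a treatment decision, not a state of the patient, and that decision is governed differently in each arm. Two opposite errors are possible.

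- **Under-count in the TTV-guided arm.** A control patient with a mild infection can have TAC lowered under local standard on any day, and so becomes an event. A comparable patient in the TTV-guided arm cannot have the target lowered between visits, and at the visit the TTV result decides.
- **Over-count in the TTV-guided arm.** A target step-down ordered by TTV may coincide with a mild infection and be recorded as a dose reduction during that adverse event. Section 3.2 gives no rule for separating this from a reduction that the infection required.

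The primary test is non-inferiority on a risk difference. A net under-count in the TTV-guided arm moves the estimate towards the claim and weakens control of the one-sided error. A net over-count costs power. Blinding the assessors does not remove a difference that is already in the data they are given.

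**Working it through.** **Which infections are affected.** Only those that meet neither 1a nor 1b.

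| Situation | TTV-guided arm | Control arm |
|---|---|---|
| Infection outside 5.7.5, between visits: lower TAC target | Not available while TTV guidance continues (5.7.3) | Local standard (5.7.6) |
| Same infection, at a study visit | TTV rule decides (5.7.2) | Local standard |
| Severe infection | Investigator may leave guidance, or choose the target when TTV indicates no change or a step up (5.7.5) | Local standard |
| Relevant BK virus infection | TAC or antimetabolite reduction preferred, depending on TTV (5.7.5) | Local standard |
| Antimetabolite or steroid reduction | Not TTV-guided (5.7.7) | Not TTV-guided (5.7.7) |

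The arms differ in the first two rows. BK virus matters for another reason: the responses named in 5.7.5 are reductions and optional IVIG, none of them an antimicrobial. An outpatient case managed that way therefore enters the endpoint through 1c.

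**Inputs for the size** (section 10.2): one-sided alpha 2.5%, margin 10 points, rates 30% (TTV-guided, pT) and 40% (control, pS), 120 per arm before drop-out and 130 after.

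**Formula.** P(conclude non-inferiority) = Φ[(0.10 − (pT − pS))/SE − 1.96], with SE = √[pT(1 − pT)/n + pS(1 − pS)/n].

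**The plan's own figure.** With n = 120, SE = √[(0.21 + 0.24)/120] = 0.0612. Then 0.20/0.0612 − 1.96 = 1.306 and Φ = 0.904. This reproduces the stated 90.42%, so the sample-size arithmetic is not in question.

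**Illustration.** The share of patients whose only event is by 1c is not in the documents. A net miscount of k points in the TTV-guided arm is assumed, with k from 1 to 5.

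- *Under-count at the margin:* true rates 50% vs 40%, observed pT = 0.50 − k, n = 130. For k = 0.05, SE = √[(0.2475 + 0.24)/130] = 0.0612, 0.05/0.0612 − 1.96 = −1.143 and Φ = 0.126.
- *Over-count under the planning assumption:* observed pT = 0.30 + k, pS = 0.40, n = 120. For k = 0.05, SE = √[(0.2275 + 0.24)/120] = 0.0624, 0.15/0.0624 − 1.96 = 0.443 and Φ = 0.671.

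| k (points) | One-sided error, under-count, n = 130 | Power, over-count, n = 120 |
|---|---|---|
| 0 | 2.5% | 90.4% |
| 1 | 3.6% | 87.1% |
| 2 | 5.1% | 83.0% |
| 3 | 7.1% | 78.3% |
| 5 | 12.6% | 67.1% |

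The choice of n matters little. With 120 per arm the error runs from 3.6% to 12.0%. With 130 per arm the power starts at 92.5% and runs from 89.5% to 70.6%.

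**The case against.** A reader might infer that 1c cannot be met in the TTV-guided arm because TAC reduction is barred there. The documents do not support that. Criterion 1c covers any immunosuppression, so reducing the antimetabolite or steroid satisfies it in both arms. Between visits, TAC dose may still move towards the current target (5.7.3). Severe infection, relevant BK virus infection and investigator judgement all open an exit (5.7.5, 6.21).

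Nor can the figure in section 5.7 be read as the frequency of step-downs. That an upper cut-off of 7.6 log10 c/mL "scored 38% of the samples above the range" describes an earlier cohort without TTV guidance, measured with the Vienna in-house assay. In the trial, guidance aims to bring TTV into range, and section 5.7.4 expects a gentle decline towards month 12.

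It would also go too far to say that the assessors cannot tell the two kinds of reduction apart. The infection must require the reduction, the medication record holds doses and schedules, and assessors may query the site and ask for investigator commentaries to be unlocked (6.17). Likewise, section 6.19 does not flatly contradict 5.7.3: it is a general statement, and section 5.6 places TAC in the active group under 5.7. The two are unreconciled for this case.

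The residual group may be small: infections that are neither severe nor relevant BK virus infection, need no admission or antimicrobial, and are managed by lowering TAC. That is fair, and nothing in the documents sizes the group. What remains is that the TAC route to 1c differs by arm, the unblinded investigator makes and records the reduction, and 3.2 has no explicit attribution rule. The analyses listed in 10.3.1, 10.3.3 and 10.3.7 do not test the effect. The severe-infection secondary endpoint isolates inpatient and day-care treatment, and so drops 1b events as well.

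**Conclusion.** The point holds in a limited form. For infections meeting neither 1a nor 1b, following the plan as written allows 1c to be counted differently by arm, in either direction. The net direction and the number of 1c-only events cannot be determined from the documents. The error range of 3.6% to 12.6% and the power range of 87% to 67% rest on an assumed net shift of 1 to 5 points. They also assume that the shift is not offset by antimetabolite or steroid reduction, by exit from guidance, or by the opposite error. They show how sensitive the test is to such a shift and do not predict that one will occur. The matter should be addressed, but it does not call for a new primary endpoint or a changed decision rule.

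**What to change.** 1. Add to section 10.3.3 a supportive sensitivity analysis of the primary risk difference that removes, in both arms, infections qualifying by 1c alone. Keep relevant BK virus infection by the protocol's own threshold (at least 10^4 c/mL or the corresponding U/mL in plasma, or biopsy-proven nephropathy), whatever drug was reduced. The primary decision rule stays unchanged: requiring both analyses to succeed would add a second hurdle and cost power.

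2. Record in the eCRF, in both arms, the reason for each reduction of immunosuppression (TTV or trough target, infection, other). Leave the attribution to infection with the blinded assessors. The unblinded site should not filter which reductions they see, since that would bring allocation knowledge into the endpoint.

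3. Reconcile sections 3.2 (1c), 5.7.3, 5.7.5 and 6.19 for infections outside 5.7.5. Which clinical rule should apply is for the sponsor and investigators to decide.

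The cost is one eCRF field, wording for the assessors and one extra analysis. The downside is slightly fewer events in that analysis.
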